### **5.3.3 Monitoring of dose administration**

Dose reductions during treatment should be based on adverse events. Oxaliplatin administration does not require hyperhydration. In the event of extravasation, administration must be discontinued immediately. For nausea and vomiting, 5-HT3 antagonists with or without dexamethasone are strongly recommended for oxaliplatin-based chemotherapy. Oxaliplatin must be infused either by peripheral vein or central venous line over 2 hours. The infusion line must be adequately flushed with 5% dextrose solution (D5W) between oxaliplatin infusion and the administration of any other drug. If desired, oxaliplatin can be administered concurrently (via a Y-connector from separate bags and lines) with leucovorin, given as a 2-hour IV infusion in 250 ml dextrose 5%, but should not be administered concurrently with 5-FU.

### **5.3.4 Accountability and dispensation**

General Accountabilities and each dispensation of FOLFOX should be recorded on the pharmacy drug accountability logs and patient accountability log of the study and should be kept in the pharmacy files. General accountabilities and dispensation of FOLFOX to each subject (dose, lot number, dates etc..) will be verified by the clinical research associate during monitoring visit at the pharmacy.

### **5.3.5 Disposition of unused investigational study drug**

The site will account for all FOLFOX study drugs dispensed and also for appropriate destruction. Certificates of delivery and destruction must be signed and a destruction certificates should be provided and signed for each FOLFOX drug destruction.

## **6. TREATMENT PLAN**

### **6.1 Subject enrollment**

#### **6.1.1 Procedures for enrolment**

After the patient signed the informed consent form and the investigator has validated all the inclusion/exclusion criteria, eligible patient will be included. The principal investigator will perform the enrollment via Tenalea system. In return, the corresponding Centre will receive via email, confirmation of the inclusion of the subject with inclusion number allocated to the patient. In case of problem with the e-randomization, the Data management department of the Centre Georges François Leclerc in charge of the inclusion could be contacted. Contact details are summarized below:

Unité de Méthodologie, Biostatistiques et Data Management  
From Monday to Friday from 9A.M to 6 P.M  
[contact] - [contact]

#### **6.1.2 Procedures for handling subjects incorrectly enrolled**

Subjects who are incorrectly enrolled and have not completed 2 Cycles of treatment will be replaced.

Subjects who have been enrolled, in spite of not meeting all the inclusion/exclusion criteria will not be replaced, data analyses will take them into account (both intention to treat and per protocol analysis).

To limit this incorrectly enrolled patients, inclusion criteria will be checked using an inclusion base before inclusion in the escalation dose phase and before inclusion in the expansion cohort.

## **6.2 Dose Modification and Toxicity Management**

### **6.2.1 Durvalumab and tremelimumab**

For adverse events (AEs) that are considered at least partly due to administration of durvalumab the following dose adjustment guidance may be applied:

- Treat each of the toxicities with maximum supportive care (including holding the agent suspected of causing the toxicity where required).
- If the symptoms promptly resolve with supportive care, consideration should be given to continuing the same dose of durvalumab or tremelimumab along with appropriate continuing supportive care. If medically appropriate, dose modifications are permitted for durvalumab and tremelimumab (see Appendix 1).
- All dose modifications should be documented with clear reasoning and documentation of the approach taken.

Investigators should exercise clinical judgment in managing actual patients alongside the guidelines presented in the protocol(s). An event that exhibits rapid progression and/or the likelihood for high morbidity/mortality requires that clinical judgment be exercised above and beyond toxicity management guidelines to ensure that treatment is optimally tailored to any given patient's specific case. For example, the general principles outlined in the toxicity management guidelines describe prompt initiation of corticosteroids for both Grade 2 events (that have persisted for 4-5 days) and Grade 3-4 events; clinical judgment applied to this baseline guidance for an event that exhibits rapid progression and/or the likelihood for high morbidity/mortality – such as myocarditis – would warrant prompt initiation of high-dose corticosteroids without delay even for grade 2 cases. Similarly, clinical judgment for patients with suspected myocarditis should lead investigators to obtain a cardiology consult and institute a thorough diagnostic work-up (that includes exclusion of other alternate causes such as infection), and the appropriate management that includes discontinuing drug (permanently if biopsy-proven immune-mediated myocarditis) and, as already noted, the prompt use of steroids or other immunosuppressives

In addition, there are certain circumstances in which durvalumab or tremelimumab should be permanently discontinued.

Following the first dose of durvalumab or tremelimumab, subsequent administration of durvalumab or tremelimumab can be modified based on toxicities observed (see Appendix 1). Dose reductions are not permitted.

Based on the mechanism of action of durvalumab or tremelimumab leading to T-cell activation and proliferation, there is the possibility of observing immune related Adverse Events (irAEs) during the conduct of this study. Potential irAEs include immune-mediated enterocolitis, dermatitis, hepatitis, and endocrinopathies. Subjects should be monitored for signs and symptoms of irAEs. In the absence of an alternate etiology (e.g., infection or PD) signs or symptoms of enterocolitis, dermatitis, hepatitis, and endocrinopathy should be considered to be immune-related.

Dose modification recommendations and toxicity management guidelines for immune-mediated reactions, for infusion-related reactions, and for non-immune-mediated reactions are detailed in Appendix 1.

In addition, management guidelines for adverse events of special interest (AESIs) are detailed in Section 10.1.3. All toxicities will be graded according to NCI CTCAE v4.03

### **6.2.2 FOLFOX (5-Fluorouracil + oxaliplatin)**

All toxicities will be recorded on the flow sheet and appropriately graded according to CTCAE Version 4.03 criteria, as regard to severity and whenever possible in relationship to drug or disease. Guidelines to be followed in the case of a deviation from treatment schedule (i.e. treatment interruption or dose modification due to an adverse event) are specific for each treatment regimen, and are described in the following subsections.

- For toxicities which are considered by the investigator unlikely to develop into serious or life threatening events (e.g. alopecia, altered taste etc.), treatment will be continued at the same dose without reduction or interruption. In addition, no dose reductions or interruptions will be required for anaemia (non-haemolytic) as it can be satisfactorily managed by transfusions
- If, in the opinion of the investigator, a toxicity is considered to be due solely to one drug (e.g. neurotoxicity due to oxaliplatin), the dose of the other drugs does not require modification.
- Dose modifications for isolated abnormal hematologic lab values will be based on haematological parameters at start of a treatment cycle. There is no scheduled sampling during a treatment cycle and thus, no scheduled collection of nadir values.

#### **Oxaliplatin-induced neurotoxicity:**

##### **Peripheral neuropathy:**

Oxaliplatin is consistently associated with two types of peripheral neuropathy: paresthesia and dysesthesia of the hands and feet (chronic), and peri-oral region (early onset). Patients treated with oxaliplatin in this study will be counselled to avoid cold drinks and exposure to cold water or air, especially for 3 to 5 days following oxaliplatin administration. For peripheral neuropathy, the scale reported in the following table will be used to determine dose adjustments.

**Laryngopharyngeal dysesthesia:**

An unusual laryngopharyngeal dysesthesia, a sensation of loss of breathing (acute respiratory distress) without any objective evidence of respiratory distress (hypoxia, laryngospasm, or bronchospasm), also has been observed. This neurotoxicity may be induced or exacerbated upon exposure to cold. If a patient develops laryngopharyngeal dysesthesia, the patient's oxygen saturation should be evaluated via a pulse oximeter and, if normal, reassurance, a benzodiazepine or other anxiolytic agent should be considered and the patient should be observed in the clinic until the episode has resolved. The oxaliplatin infusion may then be continued at 1/3 of the previous rate. Because this syndrome may be associated with the rapidity of oxaliplatin infusion, subsequent doses of oxaliplatin should be administered as 6-hour infusions (instead of the normal 2-hour infusion). Patients on oxaliplatin should not receive cold drinks or ice chips on Day 1 of each cycle as this may exacerbate oral or throat dysesthesia, as well as laryngopharyngeal dysesthesia. Administration of prophylactic medication such as Mg++, Ca++ infusions or others is at the discretion of the investigator (1g Ca-gluconate and 1g Mg-sulfate in 100 ml D5W over 15 to 30 min immediately before and after oxaliplatin). Note: administration of 5-FU must be postponed until the end of oxaliplatin infusion. If oxaliplatin has to be stopped because of neurotoxicity, 5-FU and LV or capecitabine should be administered as per protocol and for the duration required by randomization, i.e. 3 or 6 months.

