**Study Design:**

Multicentric, non randomized, prospective, phase Ib/II study.

**Step 1:** Phase Ib with the aim to confirmed the safety of the association of Durvalumab (q2w 750mg) + Tremelimumab (q4w 75mg) + FOLFOX

**Step 2:** Phase II with the aim to assess efficacy of the association of Durvalumab (q2w 750mg) + Tremelimumab (q4w 75mg) + FOLFOX

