**Figure 1a: Schedule of assessment for principal study – Association phase**

| Assessments to be performed
at the times stipulated in the
table and as clinically required
in the management of the subject | Scree-ning
(J-28 à J-1) | FOLFOX + Durvalumab (MEDI4736) +
Tremelimumab |    |    |    |    |    |    |    |
|---------------------------------------------------------------------------------------------------------------------------------------|----------------------------|--------------------------------------------------|----|----|----|----|----|----|----|
|                                                                                                                                       |                            | V1                                               | V2 | V3 | V4 | V5 | V6 | V7 | V8 |
|                                                                                                                                       |                            | Month                                            | M1 | M2 | M3 | M4 |    |    |    |
| Written informed consent/assignment of subject
identification number                                                               | X                          |                                                  |    |    |    |    |    |    |    |
| Demography and history of tobacco and alcohol use                                                                                     | X                          |                                                  |    |    |    |    |    |    |    |
| Previous treatments for colo-rectal cancer                                                                                            | X                          |                                                  |    |    |    |    |    |    |    |
| Verification of eligibility criteria                                                                                                  | X                          |                                                  |    |    |    |    |    |    |    |
| Inclusion of the subject                                                                                                              | X                          |                                                  |    |    |    |    |    |    |    |

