| QLQ-C30 and QLQ-CR29                                                                                                                  | X                          |                                                  | X  |    |    |    | X  |    |    |
| Durvalumab (750 mg)                                                                                                                   |                            | X                                                | X  | X  | X  | X  | X  | X  | X  |
| Tremelimumab (75mg)                                                                                                                   |                            | X                                                |    | X  |    | X  |    | X  |    |
| FOLFOX administration                                                                                                                 |                            | X                                                | X  | X  | X  | X  | X  |    |    |

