**Figure 1b: Schedule of assessment for principal study – Maintenance phase**

| Assessments to be performed
at the times stipulated in the
table and as clinically required
in the management of the subject | Durvalumab (MEDI4736) alone                 |     |     |     |     |     |     |     |     |     |     |     |     |     |     |     |     |     |     |     |     |     |     |     |
|---------------------------------------------------------------------------------------------------------------------------------------|---------------------------------------------|-----|-----|-----|-----|-----|-----|-----|-----|-----|-----|-----|-----|-----|-----|-----|-----|-----|-----|-----|-----|-----|-----|-----|
|                                                                                                                                       | V9                                          | V10 | V11 | V12 | V13 | V14 | V15 | V16 | V17 | V18 | V19 | V20 | V21 | V22 | V23 | V24 | V25 | V26 | V27 | V28 | V29 | V30 | V31 | V32 |
|                                                                                                                                       | M5                                          |     | M6  |     | M7  |     | M8  |     | M9  |     | M10 |     | M11 |     | M12 |     | M13 |     | M14 |     | M15 |     | M16 |     |
| Written informed consent/assignment of subject identification number                                                                  |                                             |     |     |     |     |     |     |     |     |     |     |     |     |     |     |     |     |     |     |     |     |     |     |     |
| Demography and history of tobacco and alcohol use                                                                                     |                                             |     |     |     |     |     |     |     |     |     |     |     |     |     |     |     |     |     |     |     |     |     |     |     |
| Previous treatments for colo-rectal cancer                                                                                            |                                             |     |     |     |     |     |     |     |     |     |     |     |     |     |     |     |     |     |     |     |     |     |     |     |

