### **5.2 Dose and treatment regimens**

#### **5.2.1 Treatment regimens**

##### **Durvalumab + tremelimumab**

Patient will receive 750mg durvalumab via IV infusion q2w for up to 8 doses/cycles and 75 mg tremelimumab via IV infusion q4w for up to 4 doses/cycles, and then continue 750mg durvalumab q2w starting on Week 16 for up to 20 months (40 doses). Dosing outside the window should be discussed with the Study Physician. Tremelimumab will be administered first. Durvalumab infusion will start approximately 1 hour after the end of tremelimumab infusion. The duration will be approximately 1 hour for each infusion. A 1-hour observation period is required after the first infusion of durvalumab and tremelimumab. If no clinically significant infusion reactions are observed during or after the first cycle, subsequent infusion observation periods can be at the Investigator's discretion.

(suggested 30 minutes after each durvalumab and tremelimumab infusion). FOLFOX will be administered last and will be delivered as standard practice q2w.

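### After an oxaliplatin stop for neurotoxicity, section 6.2.2 offers capecitabine, which has no regimen in the protocol, for a randomised duration that does not exist; the FOLFOX duration to fall back on is not stated consistently

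*Protocol*

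**What the plan says.** The instruction stands in the Protocol, section 6.2.2, under laryngopharyngeal dysesthesia, but it covers any stop of oxaliplatin for neurotoxicity: "5-FU and LV or capecitabine should be administered as per protocol and for the duration required by randomization, i.e. 3 or 6 months". The synopsis describes the trial as "Multicentric, non randomized, prospective, phase Ib/II study", with one regimen.

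Other places that bear on the instruction:

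- **Dose of the remaining drugs.** Where a toxicity is due solely to one drug, section 6.2.2 says "the dose of the other drugs does not require modification". Section 5.3.2 gives the 5-FU and LV doses.
- **Allowed therapy.** Section 7.2.2 names durvalumab, tremelimumab and FOLFOX as the allowed protocol therapies and excludes other concurrent chemotherapy.
- **FOLFOX interval.** Section 5.2.1: "FOLFOX will be administered last and will be delivered as standard practice q2w".
- **FOLFOX duration.** In Figure 1a the row "FOLFOX administration" is marked at V1 to V6 and blank at V7 and V8, under a column header over V1 to V8 that names FOLFOX with both antibodies. Section 5.2.2 gives 4 months (M1 to M4) for the association including FOLFOX, and 3 months of FOLFOX at retreatment. Section 5.3.2 expects 1 to 12 cycles, equated with 6 months.
- **What follows.** Figure 1b heads the visits from V9 "Durvalumab (MEDI4736) alone". Section 5.2.1 starts this phase at Week 16.

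**The concern.** This is an operative treatment instruction, and two parts of it cannot be carried out as written. No randomised duration exists to look up. The reference to the protocol leads nowhere for capecitabine: the regimen, the supply section (5.3.1) and the dose-adjustment tables cover 5-FU, LV and oxaliplatin only. A site that chose capecitabine would be adding an unspecified regimen to durvalumab and tremelimumab.

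The trigger is foreseeable. Section 6.2.2 describes neuropathy as a consistent effect of oxaliplatin, and its neurologic toxicity table has several cells that stop treatment.

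A site that ignores the stray words and continues 5-FU/LV has a dose but needs a stop date. The sections it would consult do not agree. The same disagreement bears on whether patients without toxicity receive FOLFOX at V7 and V8.

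**Working it through.** **1. Is there a regimen for each branch?** For 5-FU/LV, yes: section 5.3.2 gives the doses and the section 6.2.2 tables give reductions. For capecitabine, no: it is named only in the sentence quoted, and section 7.2.2 does not list it as allowed.

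**2. Can the duration clause be resolved?** Not from the design, because nobody is randomised. Section 5.3.2 equates 12 cycles with 6 months. This reproduces with two-week cycles and the schedule's two visits per month: 12 × 2 = 24 weeks, and 24 / 4 = 6 months. On the same scale 3 months is 6 cycles. The clause therefore means 6 or 12 cycles and does not choose between them.

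**3. What do the other sections imply?** Cycles × 2 gives weeks; weeks / 4 gives months.

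| Source | Cycles | Weeks | Months |
|---|---|---|---|
| Figure 1a row, V1 to V6 | 6 | 12 | 3 |
| Section 5.2.2, retreatment | 6 (from 3 months) | 12 | 3 |
| Section 5.2.2, association M1 to M4 | 8 (inferred) | 16 | 4 |
| Section 5.3.2, upper end of expected range | 12 | 24 | 6 |

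No section states 8. It follows only if FOLFOX is given every two weeks through all four months. The reading of the row as V1 to V6 is supported by the tremelimumab row, whose marks fall at V1, V3, V5 and V7 as a four-weekly drug requires.

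**4. Overlap with durvalumab alone.** Cycle k starts at week 2(k − 1):

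- cycle 6: 2 × 5 = week 10
- cycle 8: 2 × 7 = week 14
- cycle 9: 2 × 8 = week 16
- cycle 12: 2 × 11 = week 22

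If 12 cycles were one initial course, cycles 9 to 12 (four cycles) would start in the phase defined as durvalumab alone.

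**5. Effect on one patient.** Assume oxaliplatin stops after cycle 4; this is an illustration, not a figure from the Protocol. The fluoropyrimidine cycles left are 6 − 4 = 2 by the schedule row, 8 − 4 = 4 by the inferred four-month reading, and up to 12 − 4 = 8 by the upper end of section 5.3.2.

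**6. Effect on the 3-month decision.** Planned cycles starting before week 12 are those at weeks 0, 2, 4, 6, 8 and 10. That is six under the 6-, 8- and 12-cycle readings, so the choice of duration does not change planned FOLFOX before the 3-month assessment.

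**The case against.** The best case against the point is that the Protocol already answers the question well enough. The Figure 1a row is the only visit-by-visit statement and gives six cycles. The retreatment text agrees and says that retreatment follows the same guidelines as the initial period. The column header also names tremelimumab, which is not given at every visit, so it need not mean FOLFOX at every visit. Section 5.3.2 states an expectation that includes six, and its maximum could cover an initial course plus the one permitted retreatment: 6 + 6 = 12. On capecitabine, the reference to the protocol and the exclusions in section 7.2.2 leave 5-FU/LV as the only branch with a protocol basis.

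Much of this stands. Six cycles is the best-supported reading, 8 is an inference, and the overlap with durvalumab alone depends on reading 12 cycles as one initial course. Two things remain. Section 5.2.2 still describes a 4-month association with FOLFOX against a row that stops at V6, and section 5.3.2 does not say that its maximum includes retreatment. And the exclusions in section 7.2.2 do not cure the stray instruction; they conflict with it.

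Some stronger readings are tempting and are not supported:

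- A reader might infer three competing planned cycle numbers. The Protocol gives one marked row, one phase label and one expected range.
- A reader might infer that the primary result is compromised. The six planned cycles before week 12 are common to all three readings.
- A reader might infer that the per-protocol set cannot be defined. It consists of patients who received every planned dose, so the FOLFOX number feeds into it, but it is a repeat analysis whose detail may properly sit in an analysis plan that is not shown. The effect is secondary.

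**Conclusion.** The point holds as a correction to a treatment instruction. The sentence in section 6.2.2 cannot be followed as written: one of its two drug options has no regimen, and its duration clause refers to a randomisation that the trial does not have. The wording looks carried over from another protocol. That is an inference about its origin, and the conclusion does not depend on it.

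The FOLFOX duration is stated inconsistently, but less sharply than a bare list of 6, 8 and 12 cycles suggests. The schedule row and the retreatment text point to six; the 4-month label and the 12-cycle upper end do not match them unless explained.

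The number of patients who would receive capecitabine cannot be derived from the Protocol and is probably small. The cycle number is relevant to any of the 57 planned patients still on treatment at V7, although the schedule row gives sites a usable answer. Sample size, Simon boundaries and the 3-month decision are untouched. The correction should be made because it changes what patients are given.

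**What to change.** In section 6.2.2, delete the capecitabine option and the clause that ties duration to randomisation. State instead that 5-FU/LV continues for the remaining scheduled FOLFOX cycles at the patient's current dose, meaning the section 5.3.2 dose with any reductions already made under section 6.2.2. Referring to the section 5.3.2 dose alone could be read as restoring full dose in a patient already reduced for, say, diarrhoea or stomatitis.

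State one FOLFOX cycle number in Figure 1a (header and row), section 5.2.2 and section 5.3.2. Six fits the schedule row and the retreatment text; the sponsor should confirm it. Section 5.3.2 should also say whether its maximum of 12 cycles includes retreatment. The same number then serves for the FOLFOX part of the per-protocol definition.

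The cost is a set of wording corrections in one amendment, with no change to sample size or Simon boundaries.
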